### Statistical Analysis

Stata 16.0 will be used for statistical analysis. The distribution of categorical variables will be described by frequencies and percentages, and continuous variables conforming to normal distribution will be described by means (SDs). Chi-square tests will be performed to compare the differences between different groups. The *t* test or 1-way ANOVA will be performed to compare the mean scores between groups on the same continuous and dependent variables. Logistic regression will be conducted to analyze the factors associated with HPV vaccine hesitancy. Repeated measurement data at baseline; postintervention; and 1 week, 1 month, and 3 months after the intervention will be analyzed using generalized estimation equations (GEEs). Significant variables will be included in baseline chi-square analysis, and we will also assess group (intervention and control), time (baseline; immediately after the intervention; and 1 week, 1 month, and 3 months after the intervention), and time×group interactions, with the interaction indicating a differential change by group from baseline to the end of the trial. Statistical significance will be set at *P*<.05 (2-sided).

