Chinese authorities approved HPV vaccines in 2016 [14]. Since 2020, some provinces and cities in China, especially those with good financial status, such as Guangdong Province and Fujian City, have launched free HPV vaccination programs for school-age girls [15]. However, without supportive government policies, the high price and supply shortage of HPV vaccines have impacted accessibility and affordability in the central and western regions of China [16,17]. In addition to the financial considerations and accessibility issues, vaccine hesitancy is also a major barrier to vaccine coverage [18]. Vaccine hesitancy is defined as the refusal or delay of vaccination when immunization services are available, which means low vaccine acceptance despite the availability of vaccination services [16]. Given the young age of the HPV vaccine target population, this study will focus on HPV vaccine hesitancy among the parents of girls aged 9-14 years. A recent study in mainland China reported that 53.9% of the guardians of secondary school girls aged 12-19 years were HPV vaccine hesitant, mainly because of a lack of knowledge of HPV vaccines and insufficient communication from reliable sources of information [19]. Previous studies have demonstrated that health interventions targeting parents can effectively improve vaccine coverage among girls. In 2018, an intervention using health education manuals and reminder letters was implemented among parents of 11-12-year-old girls in New York State, which increased the HPV vaccination rate from 24.1% to 75% [20]. Research on East African immigrant mothers conducted 10 HPV vaccine–related health education forums to increase HPV vaccine–related knowledge, improve attitude, and increase the intention to vaccinate adolescent children. Results from this study showed that mothers who attended the forums showed a more positive attitude and an intention to getting their daughters vaccinated [21]. Therefore, vaccine hesitancy has been shown to be a major obstacle to HPV vaccination among targeted girls.

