**Figure 1 figure1:**
[figure not shown]
Framework of the IMB model used in the study. HPV: human papillomavirus; IMB: information-motivation-behavioral skills.

We hypothesize that a digital HPV vaccination education intervention based on the IMB model will motivate parents to vaccinate their children against HPV, thus significantly improving the local HPV vaccination rate among 11-13-year-old girls (who are in the senior grade of primary school). Therefore, the primary objective of this study is to improve the HPV vaccination rate among 11-13-year-old girls in central and western China. Through this study, we aim to explore the potential influencing factors and mechanisms of parents’ hesitancy to vaccinate their daughters against HPV. In addition, we will discuss the intervention effects of 7-day digital HPV vaccination education based on the IMB model on the parents. The ultimate goal is to evaluate the efficacy of such intervention measures against HPV vaccine hesitancy in order to help improve the HPV vaccination rate among 11-13-year-old girls in China in the future.

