## Methods

### Trial Design

This will be a double-blind randomized controlled trial (RCT) of an intervention based on an online applet. Before the intervention, the research team will carry out free HPV vaccination pilot projects for 11-13-year-old girls in 4-5 study sites in low-health-resource areas in China. After the first stage of the HPV vaccination program is completed, 11-13-year-old girls’ parents who choose not to vaccinate their daughters will be invited to our intervention study, and those who are willing to participate will be guided to register and log on to the “Yi Yan Health” mini applet (Figure 2), which was independently developed by our research team and can be used for mobile app–based education and questionnaire collection. Next, all participants will be randomly divided into 2 groups: (1) an intervention group, which will receive a baseline questionnaire, 7-day digital HPV vaccination education based on the IMB model (with a sample shown in Figure 3), and follow-up right after the intervention period and 1 week, 1 month, and 3 months after the intervention, and (2) a control group, which will only receive popular science education that is not related to HPV vaccines; these non-HPV publicity materials will be uploaded at the same time every day as the intervention group to maintain parents’ interest in the control group. Meanwhile, participants in the control group will also need to complete questionnaires simultaneously with the intervention group. After the intervention trial, we will provide the control group with the same IMB-based HPV vaccine intervention materials free of charge for ethical considerations. Our free HPV vaccination pilot program will also continue until at least half a year after the intervention to ensure that all 11-13-year-old girls whose parents are willing to vaccinate their daughters can receive the first HPV vaccination during or after the intervention.

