#### Secondary Outcomes: Parents’ Hesitancy and Attitudes Toward HPV Vaccines

We will measure parents’ hesitancy and attitudes toward HPV vaccines in 3 parts. The first part is about general vaccination attitudes, which will be used to investigate participants’ attitudes toward other common vaccines recommended by the Chinese government. The second part is about HPV vaccine hesitancy, which will be used to assess the degree of HPV vaccine hesitancy among parents. The third part is about vaccine confidence used, which will be to investigate participants’ confidence in HPV vaccines.

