## Discussion

### Summary

This multicenter RCT based on an online mini applet aims to reduce vaccine hesitancy among parents of 11-13-year-old girls in central and western China by using digital education measures based on the IMB model. By reducing vaccine hesitancy, the intervention will encourage parents to vaccinate their daughters against HPV, improve the coverage of HPV vaccines in China, and promote the elimination of cervical cancer in China. To the best of our knowledge, this study will be the first to evaluate whether the mobile app–based education intervention designed according to the IMB model can improve the HPV vaccination rate among 11-13-year-old girls in central and western China. In addition, this study will also explore the factors associated with parents’ HPV vaccine hesitancy, which may provide a much clearer reference for formulating an HPV vaccination policy and subsequent HPV vaccination rate intervention studies in China.

Our study will focus on girls in central and western China because the distribution of health resources in China is still not completely balanced, and the central and western regions have relatively fewer resources than the east [33,34]. Due to relatively scarce health resources, 11-13-year-old girls in central and western China are less knowledgeable about HPV and HPV vaccines [35]. In addition, compared to some eastern provinces of China, such as Guangdong, Fujian, and Shandong Provinces, which have launched free HPV vaccination campaigns for 11-13-year-old girls, it is much more difficult for girls in central and western China to obtain HPV vaccines. Therefore, it is more urgent and significant to carry out vaccination campaigns and intervention studies in central and western China to realize the target of eliminating cervical cancer in the country.

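### The hesitancy regression uses only parents who have already refused, so it can describe differences among refusers but not what separates hesitant from accepting parents

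*Protocol article*

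**What the plan says.** The Introduction gives the protocol's only definition of the concept: "Vaccine hesitancy is defined as the refusal or delay of vaccination when immunization services are available". Its closing paragraph sets an aim on that basis: "we aim to explore the potential influencing factors and mechanisms of" parental hesitancy. The Discussion (Summary) repeats it, saying that "this study will also explore the factors associated with parents" hesitancy, and adds that the findings may inform vaccination policy and later intervention studies.

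The sample is fixed in Trial Design, where "parents who choose not to vaccinate their daughters will be invited to our intervention study". Eligibility Criteria makes refusal of the offered first dose the first inclusion criterion. No section describes a survey of parents who accepted.

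The analysis is one sentence in Statistical Analysis: "Logistic regression will be conducted to analyze the factors associated with HPV vaccine hesitancy". It names no time point and no coding of the outcome. Under Secondary Outcomes, one questionnaire part measures hesitancy on a graded basis, "which will be used to assess the degree of HPV vaccine hesitancy among parents". The candidate factors (information, motivation and behavioural skills, plus reasons that parents give directly) appear under Other Outcomes.

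**The concern.** To learn what goes with being hesitant, an analysis needs both hesitant and non-hesitant parents. This trial recruits on the very behaviour that its Introduction calls hesitancy. That suits a trial of an intervention to change refusers' minds, but it removes the comparison that the exploratory aim implies.

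What is at stake is how the odds ratios are read. A policy reader told that certain factors go with parental hesitancy will take them as features that distinguish refusing from accepting families. Here they would describe differences within refusers, which may be weaker, or simply different. The Limitations section mentions convenience selection of sites and incomplete follow-up of the dose series, but not this restriction.

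**Working it through.** The document gives no figure for this analysis. Its one calculated figure, 74 per group, belongs to the primary comparison and does not enter here. The check is therefore mainly a comparison of sections, with two short calculations.

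**Step 1: definition against population.**
- Definition (Introduction): refusal or delay when the service is available.
- Population (Trial Design, Eligibility Criteria): parents who refused the offered first dose.
- Planned size (Sample Size): 5 sites × 150 = 750.
- By this definition, 750 of 750 participants are hesitant at entry and 0 are accepting. If baseline refusal itself were the dependent variable, then p = 1, p(1 − p) = 0, and no slope could be estimated. A trial fit with a constant outcome failed with a singular matrix.

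**Step 2: outcomes that can vary in this sample.** The regression sentence does not say that baseline refusal is the outcome. Two others are available:
- the graded hesitancy score, collected with the questionnaire: "Repeated measurement data at baseline; postintervention; and 1 week, 1 month, and 3 months after the intervention will be analyzed";
- vaccination within 3 months after the intervention, checked against local health information systems (Primary Outcome).

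Both can differ among initial refusers, so a model can be fitted. The remaining difficulty is which question it answers.

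**Step 3: is such a model workable?** For one standardised predictor, SE(log OR) ≈ 1/√[n·p(1 − p)], and the OR detectable with 80% power at two-sided 0.05 is about exp[(1.960 + 0.842)/√(n·p(1 − p))]. The document does not give p, so the shares are assumed. With n = 750:
- 95% / 5% split: smaller class about 38, n·p(1 − p) = 35.6, OR about 1.60 per SD
- 90% / 10%: 75, 67.5, OR about 1.41
- 80% / 20%: 150, 120, OR about 1.29
- 50% / 50%: 375, 187.5, OR about 1.23

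The expression is symmetric in p, so the same values serve for score category or for vaccination versus continued refusal. Precision is not the obstacle.

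**Step 4: does a within-refuser model answer the wider question?** An illustration, with every input assumed: latent hesitancy is 0.5 × factor (per SD) plus logistic error; the top 30% refuse; the questionnaire score is the latent value plus standard normal noise; refusers are split at their median score.
- Refusal versus acceptance in all parents: log OR 0.51 (OR = e^0.51 ≈ 1.67)
- High versus low score among refusers only: log OR 0.10 (OR = e^0.10 ≈ 1.11)

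The same factor looks much weaker once the sample is selected on the behaviour. The size of the drop depends on the assumptions and is not an estimate for this trial. It shows only that the two questions can have different answers.

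**Step 5: follow-up data.** The intervention is designed to change information, motivation and behavioural skills (Intervention section), and those are also the candidate factors. If their post-intervention values were used as predictors, part of the association would come through the intervention. Baseline values, taken before the education starts, avoid this.

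**The case against.** The best defence is that the Introduction's definition is cited background, whereas the Methods measure hesitancy by a graded questionnaire. Refusers can differ in degree, and a baseline cross-sectional model of that degree can be estimated and is free of any treatment effect. Parents are also asked directly for their reasons, so the aim does not rest on the regression alone. The factors are listed under Other Outcomes and the wording is exploratory. Coding, cut-off and covariates of an exploratory model are details that an article may leave to a fuller plan.

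Most of this stands, and it rules out three stronger readings that a reader might infer:
- That the outcome has no variation. This is true only if baseline refusal is the dependent variable, which the document does not say.
- That the aim cannot be answered. The degree of hesitancy, later vaccination and stated reasons can all be studied among refusers.
- That the plan leaves study arm out of this regression. The sentence lists no covariates at all, and silence is not a decision to omit one.

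The defence does not supply a comparison group. No detail in a fuller analysis plan can provide accepting parents whom the design does not recruit, and the Introduction and Discussion state the aim without limiting it to refusers.

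**Conclusion.** The concern holds in a limited form and is minor. All 750 planned participants are refusers, so the logistic regression cannot identify what distinguishes hesitant from accepting parents, however the outcome is coded. It can identify correlates of stronger or weaker hesitancy, or of later vaccination, among parents who first refused. The stated aim and its suggested policy use are wider than that.

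This rests on the eligibility criteria as written and on the absence of any described survey of accepting parents. It does not depend on the illustrative simulation or on the assumed outcome shares. The randomised comparison of vaccination within 3 months is not affected.

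**What to change.** 1. In Statistical Analysis, add or substitute a logistic model of registry-verified vaccination versus continued refusal by 3 months. Use only baseline predictors (baseline information, motivation and skills scores, demographics, stated reasons), with arm and site included. Present the results as predictors of moving from refusal to vaccination.
2. If the hesitancy questionnaire score is also modelled, use baseline data and describe the results as correlates of the degree of hesitancy among refusers.
3. In the closing paragraph of the Introduction and in the Discussion summary, limit the inference to parents who had initially refused. A sentence in Limitations saying that accepting parents were not surveyed would help.

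The cost is small. The change affects the analysis specification and wording, uses data already planned, and needs no additional participants. The downside is a narrower claim.

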### Sample Size

According to the purpose of intervention effect evaluation, the comparison formula of 2 independent rates is used to calculate the required sample size. To date, there are no studies on the effects of a mobile app–based intervention for 11-13-year- old girls in central and western China to improve the HPV vaccination rate. For this reason, the anticipated effect size is largely based on findings of similar studies derived from the relevant literature in other countries. In this study, according to the literature review and the results of our research team’s free HPV vaccination campaign conducted in Ordos City, Inner Mongolia Autonomous Region, China, in 2020, about 30% of parents in the control group refused to vaccinate their daughter (Pc), while parents in the intervention group who refused are expected to be 20% lower than those in the control group (Pt): α=.05 (2-sided), β=.2 [29-31]. Considering the possible dropout (20%), the intervention and control groups need 74 effective samples each, totaling 148, and each project site needs to recruit about 150 participants. There will be 750 participants in 5 project sites, 375 (50%) in the intervention group and 375 (50%) in the control group.

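### The time-by-group interaction is read as change from baseline to the end of the trial, which is true only of the 3-month term; name that contrast, adjusted for baseline, as the end-of-trial effect

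*Protocol article*

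**What the plan says.** Under Statistical Analysis, the protocol article assigns the repeated questionnaire data to generalized estimating equations (GEE). The model has terms for group, time and their interactions. Time is listed as five points: baseline, immediately after the course, and 1 week, 1 month and 3 months later. The interaction is then given a meaning: "with the interaction indicating a differential change by group from baseline to the end of the trial". The section does not say whether time is categorical or continuous, whether the interaction is tested jointly or visit by visit, or which term supports a conclusion about the end of follow-up.

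The same section lists, among general methods, that a t test or "1-way ANOVA will be performed to compare the mean scores between groups", with no mention of the baseline score. Significance is two-sided at 5%.

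The outcomes concerned are the questionnaire scores under Secondary Outcomes: general vaccination attitudes, a hesitancy part "which will be used to assess the degree of HPV vaccine hesitancy among parents", and vaccine confidence. The primary outcome is vaccination within 3 months, checked in local health-agency systems, and is not a repeated score.

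**The concern.** Two arms and five categorical time points give (2 − 1) × (5 − 1) = 4 interaction coefficients. With baseline as the reference, each is the arm difference in change from baseline to one visit. Only the last, at 3 months, means what the sentence says. The overall test of all four asks whether the arms' profiles differ anywhere. It can reject because of a difference that exists only at the first visit after the course.

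This matters because the course lasts 7 days and follow-up runs for 3 months, so the later visits are the ones that can show whether a change in attitude persists. If the overall test is used and read as the sentence reads it, an effect that appeared and vanished could be published as an end-of-trial reduction in hesitancy.

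A lesser matter is precision. The baseline score is already collected. Neither an unadjusted comparison at 3 months nor a change-from-baseline contrast makes the best use of it.

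**Working it through.** **The plan's own figure.** The only sample-size calculation is for the binary primary outcome, with "α=.05 (2-sided), β=.2". Taking refusal as 30% against 10%, with unpooled variance: n = (1.960 + 0.842)² × (0.30 × 0.70 + 0.10 × 0.90) / 0.20² = 58.9 per group. Allowing for 20% dropout, 58.9 / 0.8 = 73.6, so 74, as stated. This reproduces but gives no power for the scores.

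**Inputs from the article.** 375 per arm and 20% dropout (Sample Size), so 375 × 0.8 = 300 per arm analysed; two-sided 5%; five time points.

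**Inputs assumed.** The article gives no scale, SD or correlation. I take scores in SD units and the same correlation ρ between any two visits, from 0.4 to 0.7. The transient effect has arm differences d = (0, 0.2, 0.1, 0, 0) SD at the five points, so it is gone by 1 month.

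**Overall interaction, 4 df.** Noncentrality λ = (n/2) × Σ(d − mean d)² / (1 − ρ).
- Mean d = 0.3/5 = 0.06, so Σ(d − mean d)² = 0.04 + 0.01 − 5 × 0.0036 = 0.032.
- λ = 150 × 0.032 / (1 − ρ) = 4.8 / (1 − ρ).
- Power is the probability that a noncentral chi-square on 4 df exceeds 9.488.

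| ρ | λ | Overall test significant | 3-month contrast significant |
|---|---|---|---|
| 0.4 | 8.0 | 60% | 5% |
| 0.5 | 9.6 | 70% | 5% |
| 0.7 | 16.0 | 91% | 5% |

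The true 3-month difference is zero, so the last column is the type I error rate. An effect of 0.2 SD at the post-course visit alone gives the same sum, 0.04 − 5 × 0.0016 = 0.032, and so the same table. With a 0.3 SD effect at that visit alone and ρ = 0.5, the formula gives 97.5%. A simulation of 4,000 trials gave 97.6% for the overall test and 4.8% for the 3-month contrast.

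**Time as a straight line.** With the 0.2/0.1 SD pattern at ρ = 0.5, a group-by-slope term is significant in 19% of trials (visit number 0 to 4) or 25% (weeks 0, 2, 3, 6.3 and 15). The slope mostly has the opposite sign to the early effect. The cause is the curved trajectory, not the uneven spacing of visits, because actual weeks can be entered.

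**Precision at 3 months.** Relative to the unadjusted t test, the variance is 1 for the t test, 2(1 − ρ) for the change contrast, and 1 − ρ² for ANCOVA. ANCOVA against the change contrast is therefore (1 + ρ)/2.

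| ρ | Reduction against t test | Reduction against change contrast |
|---|---|---|
| 0.4 | 16% | 30% |
| 0.5 | 25% | 25% |
| 0.7 | 49% | 15% |

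For a true 0.2 SD difference at 3 months, 300 per arm and ρ = 0.5, power is 69% by the t test or the change contrast and 81% with adjustment.

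**The case against.** A reader might infer that the plan specifies a joint 4-df test and will therefore misreport a transient effect. The article does not support that. It names no joint test, and it speaks of interactions in the plural. With baseline as the reference visit, the 3-month-by-group coefficient is exactly the change the sentence describes, so the sentence is right if that coefficient is the one used. The words could also be taken loosely, as the period over which the arms' profiles are compared. Nothing suggests that visit-level results would be withheld. The choice of contrast and covariates is, besides, often left to an analysis plan that is not shown here.

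Most of this stands, and it limits the point to what could happen. It does not remove the point, because the article goes beyond silence: it attaches an end-of-trial meaning to the interaction without tying it to the one term that carries that meaning.

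A reader might also infer that the listed t test is invalid, or that the plan throws the baseline score away. Neither follows. Under randomisation the unadjusted t test is unbiased. It appears in a general list and is not named as the estimator of the arm effect. GEE, the method named for the repeated data, includes baseline as a time point. What remains is a loss of precision.

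**Conclusion.** The point holds as an ambiguity with a consequence, not as a demonstrated error in the test. The stated reading is correct for the 3-month-by-group term and wrong for the overall interaction. Under the assumed transient effect, the overall test would be significant in about 60% to 91% of trials, against 5% for the contrast that answers the question. These percentages depend on the assumed effect pattern, equal correlations and 300 per arm. That the overall test responds to early differences does not depend on them.

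Baseline adjustment is a separate and smaller gain in precision. Only conclusions about the repeated continuous scores are touched; the primary comparison of vaccination is not.

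**What to change.** For each continuous secondary score:

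- State that time is categorical.
- Name the arm difference at 3 months, adjusted for the baseline score, as the 1-df effect behind any end-of-trial conclusion. Estimate it by ANCOVA, or from the longitudinal model with baseline adjustment or a common baseline mean.
- Report the earlier visits, and any joint interaction test, as supporting results.
- Reword the interpretive clause so that it refers to the 3-month contrast only.
- Do not use an unadjusted t test for the arm effect; it can stay in the general list for other comparisons.

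The cost is a few lines of analysis text, to be settled before allocation is revealed to the analysts. No new data, visits or participants are needed, because baseline scores are already collected.
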